### Baseline Testing and Randomization

Baseline testing will last approximately 150 minutes. Participants will be provided with a detailed consent form and will be invited to ask any questions. After written consent is obtained, weight, height, and blood pressure will be taken and a 7-day physical activity recall interview [44] will be conducted to confirm eligibility.

Eligible individuals will be stratified based on sex and then randomly assigned to either the HIIT or MICT exercise conditions. An external statistician, who has no other involvement in the trial, will generate random allocation sequences, which will be linked to an interactive Web page. Permuted blocks of random size will be used. Once an individual is identified as eligible, the research coordinator will access the password-protected Web page, and after entering requisite information on patient eligibility and sex, participants will be randomly allocated. Participants and researchers will be aware of group allocation. Following group assignment, participants will have a fasting blood sample taken, consume a 75 g glucose drink as part of a modified oral glucose tolerance test, complete several Web-based questionnaires, have a second blood sample taken 30 minutes following the glucose drink consumption, undergo a body composition scan, and complete a maximal cardiorespiratory fitness test to exhaustion on a cycle ergometer. At the end of the session, participants will be provided with an accelerometer to wear for 7 consecutive days, commencing the day after baseline testing. Participants will be shown how to wear the device and will be instructed to remove the device while sleeping or for water-based activities. In addition, instruction will be provided to remind participants how to correctly wear the accelerometer. Short message service (SMS) text messages or emails will be sent on days 1, 3, and 5 of monitoring to remind participants to wear the device (see Multimedia Appendix 1 for study measures).

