### Supervised Exercise Training

In this study, 10 days after completing baseline testing, eligible participants will begin the 2-week supervised exercise training. Participants in each condition will participate in 10 sessions of exercise performed over a 12-day period (ie, Monday to Friday over 2 weeks with Saturday and Sunday as rest days). Seven of these sessions will be supervised in the laboratory and will last approximately 30 to 60 minutes each, while 3 sessions will be conducted at home to foster independence and work through plausible barriers participants may encounter in the future. Each supervised exercise session will occur one-on-one with a counselor and will consist of an exercise component (ie, HIIT or MICT) and 10 minutes of counseling. Participants will be exposed to a variety of exercise formats within their given modality (ie, stationary cycling, treadmill walking, elliptical machine, and outside walking). For 4 of the 7 supervised sessions, participants will be able to self-select the exercise format to encourage autonomy. A total of 2 sessions will be performed on the cycle ergometer during which in-task affect and enjoyment will be assessed to more precisely control exercise intensity and control for the influence of exercise format on enjoyment. The exercise prescriptions for each condition will be progressive in nature (see Table 1) and matched for estimated external work.

**Table 1 table1:** Two-week intervention exercise prescription.

High intensity interval training^a^	Training day/activity completed	Continuous moderate intensity training^b^
4 intervals	Day 1^c^	20 minutes
5 intervals	Day 2^d^	29 minutes
6 intervals	Day 3^e^	33 minutes
Home day, 6 intervals prescribed	Day 4^e^	Home day, 33 minutes prescribed
7 intervals	Day 5^e^	36 minutes
8 intervals	Day 6^e^	40 minutes
Home day, 8 intervals prescribed	Day 7^e^	Home day, 40 minutes prescribed
9 intervals	Day 8^e^	43 minutes
Home day, 9 intervals prescribed	Day 9^e^	Home day, 43 minutes prescribed
10 intervals	Day 10^c^	50 minutes

^a^One high intensity interval consists of 1 minute at ~80-90% VO_2_ peak and one minute ~40% VO_2_ peak.

^b^Moderate intensity continuous exercise consists of continuous exercise at ~45-55% VO_2_ peak.

^c^Stationary bike.

^d^Outdoor walking (hills for HIIT, flat for MICT).

^e^Participant choice (includes stationary bike, treadmill, elliptical, outdoor walking).

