#### Primary Outcomes

The primary outcome is cardiorespiratory fitness determined by measuring VO_2_ peak at 6- and 12 months postrandomization. VO_2_ peak will be assessed by a continuous incremental ramp maximal exercise test on an electronically braked cycle ergometer (Lode Excalibur, The Netherlands). Expired gas will be collected continuously by a metabolic cart (Parvomedics TrueOne 2400, Salt Lake City, Utah, USA) that is calibrated with gases of known concentration and a 3.0 L syringe before every test. The test begins with a 4-minute warmup at 30 Watts, after which Watts increase by 1 every 4 seconds (15 Watts per minute). Verbal encouragement will be provided to the participant throughout the test. The test will be terminated upon volitional exhaustion or when revolutions per minute fall below 50. VO_2_ peak is defined as the highest 30-second average for VO_2_ (in L/min and mL/kg/min). Criteria for achieving VO_2_ peak are (1) respiratory exchange ratio >1.15; (2) plateau in VO_2_; (3) reaching age-predicted heart rate (HR) peak (220-age); and/or (4) volitional exhaustion. A Polar chest strap, which is integrated with the metabolic cart and cycle ergometer software (Lode Exercise Manager), will capture HR. HR peak and peak power output will be recorded as the highest values attained in the test. Cardiorespiratory fitness will be assessed at baseline and 6- and 12-month follow-up.

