#### Proposed Data Analyses

Preliminary analyses will be conducted to test for univariate and multivariate outliers and to test for normality. Data transformations will be conducted if required. Variance between the conditions in baseline outcome variables will be examined. Data will be analyzed on an intention-to-treat basis, with individuals retained within their randomized groups regardless of participation. All significance tests will be assessed at a 5% level of significance and effect sizes will be reported. Sensitivity analysis will be conducted to examine the impact of missing data. We will account for missing data by performing multiple imputation by chained equations to determine whether the results are impacted [74].

Mixed-effects regression with baseline as a covariate and 6- and 12-month outcomes as dependent variables will be used to examine differences in cardiorespiratory fitness between HIIT and MICT. Physical activity behavior assessed by accelerometer will be analyzed similarly but will include 3-, 6-, 9-, and 12-month time points. Mixed-effects regression using baseline and all other time points will be used to determine whether the treatments result in a significant change from baseline.

The mediating effects of task self-efficacy, self-regulatory efficacy, concurrent self-regulatory efficacy, outcome expectations, and self-monitoring will be examined using the INDIRECT macro developed by Preacher and Hayes [75]. The macro computes the following steps simultaneously: (1) regression coefficients for the impact of the intervention on the potential mediators; (2) the association between changes in the mediators and changes in the outcome variable; and (3) the total effects, direct effect, and indirect intervention effects. Bias-corrected bootstrapped 95% asymmetrical CIs will be computed for the indirect effect. Significant mediation will be established if the CIs do not include zero. Multiple mediation models will be computed for MVPA at 12-month follow-up and cardiorespiratory fitness at 12-month follow-up.

A series of mixed-effects regressions will be conducted to examine changes over time between groups in anthropometrics, body composition, biochemical markers, CGM, and additional psychological constructs.

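### Open allocation precedes the baseline VO2peak test, questionnaires and accelerometer week, so a reaction to allocation can enter the primary covariate and the reference for change

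*Protocol article*

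**What the plan says.** The section Baseline Testing and Randomization sets out the order of the visit. Before allocation, the only measurements are these: "weight, height, and blood pressure will be taken and a 7-day physical activity recall interview". The coordinator then obtains the allocation from a web page, and the article states: "Participants and researchers will be aware of group allocation". Next comes the sentence beginning "Following group assignment, participants will have a fasting blood sample taken". It goes on through the glucose drink, the web-based questionnaires, a second blood sample and the body scan, and ends with the instruction to "complete a maximal cardiorespiratory fitness test to exhaustion on a cycle ergometer". Participants are then "provided with an accelerometer to wear for 7 consecutive days, commencing the day after baseline testing".

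Under Primary Outcomes, the VO2peak test is run with verbal encouragement, and "The test will be terminated upon volitional exhaustion or when revolutions per minute fall below 50". Volitional exhaustion is also one of the and/or criteria for having reached VO2peak.

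Under Proposed Data Analyses, fitness is compared by "Mixed-effects regression with baseline as a covariate and 6- and 12-month outcomes as dependent variables", and accelerometry is handled similarly. A second set of mixed models uses baseline as a time point to estimate change.

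Under Supervised Exercise Training: "10 days after completing baseline testing, eligible participants will begin the 2-week supervised exercise training". No section describes a blinded tester or a VO2peak test before allocation.

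**The concern.** Adjustment for a baseline value is safe because allocation cannot have influenced it. Here that guarantee is missing for three groups of measures: the effort-dependent VO2peak test, the self-report scales and the activity week. A participant who has just been told the arm may push harder or less hard on the bike, answer differently, or change activity during the monitored week. The staff giving encouragement may also know the arm.

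The primary HIIT versus MICT contrast is at stake through its covariate. So are all change-from-baseline estimates for fitness and for accelerometer-measured activity, the outcome that set the final sample size. The mediation models use changes in the psychological scales and share the exposure.

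**Working it through.** **Inputs.** From Sample Size: mean 20.8 and SD 4.0 mL/kg/min, target difference 9%, correlation among repeated measures r = 0.5, 50 per group, 20% loss. The documents give no arm-related effort shift, so b (shift at baseline) and c (shift at follow-up) are assumptions. So is r = 0.8, used to show a range.

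**1. The plan's own figures.** Target: 0.09 × 20.8 = 1.872 mL/kg/min, and 1.872 / 4.0 = 0.468 (the article gives d = 0.48, f = 0.24). With f = 0.24, r = 0.5 and three time points (assumed), the within-between interaction calculation gives 15 per group with power 0.808, as stated. The order of allocation does not change this number.

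**2. Shift at baseline only.** With equal variances the slope on baseline is r. If one arm's measured baseline moves by b, its adjusted contrast is biased by −r × b, so extra effort at baseline counts against that arm.
- b = 0.5: 0.5 × 0.5 = 0.25 in magnitude; 0.25 / 1.872 = 13%
- b = 1.0: 0.5 × 1.0 = 0.50 in magnitude; 0.50 / 1.872 = 27%

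A simulation with no true effect (40 per group, 4000 runs) lowered the HIIT baseline by an assumed 2% to 5%, that is 0.42 to 1.04. At r = 0.5 the formula gives 0.21 to 0.52, the simulated bias was 0.22 to 0.53, and the type I error was about 6% to 11%. At r = 0.8 the formula gives 0.33 to 0.83, and the type I error was about 9% to 32%.

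**3. Shift that persists.** The follow-up tests are equally open and effort-dependent. With a follow-up shift c, the adjusted bias is c − r × b and the unadjusted bias is c. If c = b, these are b(1 − r) and b. For b = 1.0, the adjusted bias is 0.5 at r = 0.5 and 0.2 at r = 0.8, against 1.0 unadjusted. For b > 0 and c ≥ 0, adjustment gives the smaller bias whenever c > r × b / 2; at r = 0.5 that means more than a quarter of the shift persists.

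**4. Change models.** The bias in an arm's change is c − b. If only baseline shifts, b enters in full: 0.5 / 1.872 = 27% to 1.0 / 1.872 = 53% of the target. If the shift persists fully, it cancels. For activity, an assumed reaction of 2 min/day in the reference week is 2 / 10 = 20% of the 10 min/day within-group increase used for the sample size.

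**5. Can the planned look at baseline differences settle it?** With 50 per group the standard error of the baseline difference is 4.0 × √(2/50) = 0.80, so chance alone gives about ±1.57 (1.96 × 0.80). A shift of 0.5 to 1.0 lies well inside that range.

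**6. Precision lost by dropping baseline.** The residual variance rises from (1 − r²)σ² to σ². At r = 0.5 the standard error grows by 1/√0.75 = 1.15, and at r = 0.8 by 1/√0.36 = 1.67, less whatever the pre-allocation covariates recover.

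**The case against.** The strongest reply is that all the magnitudes are assumed: the documents give neither the size nor the sign of any effort difference. That stands, and the percentages above are illustrations only. It is also fair that effort need not shift only at baseline. If it shifts equally at follow-up, adjustment for the post-allocation baseline helps, and removing it does harm. That stands too, and it limits how a sensitivity analysis can be read.

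Effort can be examined in part, because the test records respiratory exchange ratio, plateau, peak heart rate and peak power. This is useful but incomplete, since volitional exhaustion alone can satisfy the criteria.

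Allocating after the accelerometer week would not be a simple reordering. Under Continuous Glucose Monitor the first 20 participants randomised are invited, and the monitor is inserted 3 days after the preassessment with 8 to 10 per group. Condition-worded scales also need either the allocation or two versions. Both points shape the remedy.

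One might say that sensitivity analyses belong in an analysis plan that is not shown. But the concern is the stated order of the visit, not a missing analysis, and no other section of the article repairs that order.

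**Conclusion.** The concern holds for VO2peak, accelerometry and self-report. The stated order lets a reaction to open allocation enter the primary covariate and the reference for change, and most of this exposure was avoidable. The illustrative size is 0.25 to 0.50 mL/kg/min (13% to 27% of the 1.87 target). It rests on an assumed baseline-only shift of 0.5 to 1.0, the plan's r = 0.5 and equal variances. With a persistent shift the adjusted bias is b(1 − r).

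A reader might infer more, but the documents do not support it:
- That every baseline measure is compromised. Fasting bloods and a body scan at the same visit are little affected by hearing the arm.
- That the bias is known to favour one arm. No direction can be derived.
- That a fitness test stopped on safety grounds is a post-randomisation withdrawal. Participant Safety says only that the test ends, and Proposed Data Analyses keeps participants in their randomised groups.
- That dropping the baseline covariate cures the problem. It can increase the bias.

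**What to change.** **For this design.** Move the web-page allocation to the end of the same baseline visit, after the VO2peak test and the questionnaires that are not worded by arm. Give the arm-worded scales after allocation, or in both versions beforehand. This adds no visit and no participants and leaves the glucose-monitor timing intact. Two versions would add 4 + 5 + 23 = 32 items (task self-efficacy, concurrent self-regulatory efficacy and outcome likelihood in Table 2).

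The accelerometer week would still follow allocation. Allocating after that week also protects it, but only if the glucose-monitor invitation goes by enrolment order instead of randomisation order and its per-group count is reconciled. It would also leave little time between the end of the 7-day week and the start of training.

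**For this trial.** Data collection ended in March 2017, so the order cannot be changed. The report should:
- state that these baseline measures followed open allocation;
- compare baseline VO2peak, respiratory exchange ratio, plateau, peak heart rate and peak power by arm;
- add a sensitivity analysis of the primary contrast adjusted only for pre-allocation data (sex, age, weight or BMI, 7-day recall).

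That analysis should be read alongside the primary model and not in its place, because it loses precision and could be the more biased of the two if the effort shift persists. The cost is one extra model, one table and one sentence of disclosure, with no new data.

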## Methods

### Study Design

*Small Steps for Big Changes* is a 2-arm, parallel group randomized controlled trial comparing adherence to HIIT with MICT in individuals at risk of T2D. This single-center trial will be conducted at The University of British Columbia, Okanagan Campus. The design of the study and flow of participants is described in Figure 1. Participants in both conditions will receive a 2-week supervised physical activity intervention consisting of engagement in their randomized exercise modality and brief, targeted counseling. The physical activity counseling will be identical for both conditions. Follow-up assessments will occur at 3, 6, 9, and 12 months. The trial will aim to recruit 100 participants. The supervised training will be conducted in waves (10 waves with approximately 10 participants per wave). All participants will begin supervised training on a Monday. Reporting of this trial protocol follows the Standard Protocol Items: Recommendations for Interventional Trials statement. Future reporting of the results of this trial will follow the Consolidated Standards of Reporting Trials guidelines [41].

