A voluntary subsample of 8 to 10 participants per group will return to the laboratory 3 days after the preassessment for insertion of a continuous glucose monitor (CGM). The CGM will be worn for 2 consecutive days, and participants will be provided with a standardized diet. Participants will return after 2 days of wearing the CGM to have the CGM removed. These 2 additional visits to the laboratory will last approximately 30 minutes in total. No sample size calculation will be conducted as this aspect of the study represents an exploratory aim to determine if CGM can be used to detect changes in glucose control in this population.

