Samples will be batch-analyzed in duplicate after storage at −80℃. Plasma glucose will be assessed via the enzymatic hexokinase method using a commercial assay (Pointe Scientific) on a clinical chemistry analyzer (Chemwell 2910, Awareness Technologies). Insulin will be measured by enzyme-linked immunosorbent assay (Mercodia, Upsula, Sweden), as described previously [65]. Glucose (mmoL/L) and insulin (mU/L) values will be used to calculate homeostasis model assessment of insulin resistance using the Web-based Homeostasis Model Assessment-2 calculator, a validated method that is highly correlated (*r*=.88) with the hyperinsulinemic-euglycemic clamp [66] and is sensitive to change following exercise interventions [65,67,68]. Oral glucose disposition index will be used to assess beta-cell function and will be calculated based on the hyperbolic relationship between glucose-stimulated insulin secretion (change in plasma insulin divided by the change in plasma glucose from fasting to 30 minutes) and insulin sensitivity (1/fasting insulin, as described by Utzschneider et al [68]). The inflammatory marker C-reactive protein will also be assessed. Postintervention samples will be obtained approximately 48 hours following the last supervised training session and at 12-month follow-up.

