##### Continuous Glucose Monitor

CGM will take place using the iPro 2 Professional CGM and Enlite sensor (Medtronic MiniMed, Northridge, CA) in a subsample of participants. The first 20 participants randomized in the trial will be invited to participate in the CGM assessment. The CGM records glucose values in a blinded fashion using a small microneedle inserted into the subcutaneous abdominal adipose tissue that is connected to a recorder that quantifies interstitial glucose values every 5 minutes. Finger-stick blood glucose samples are taken 4 times per day and are analyzed by a software program (CareLink Pro) upon device removal and downloaded to create 24-hour blood glucose curves. CGM data will be analyzed for (1) average blood glucose, (2) 2-hour postprandial area under the glucose curve, (3) postmeal spikes, and (4) glycemic variability (mean amplitude of glycemic excursions and SD). Participants who wear a CGM will be provided a standardized diet (approximately 24 kcal/kg, approximately 60% carbohydrates, approximately 27% fat, and approximately 13% protein) to consume during the day before and on the day of each 24-hour monitoring period. CGM data will be collected for 24 hours at baseline and beginning approximately 24 hours after the last day of supervised training. To accurately interpret CGM data, each participant will consume the same meals at the same times of the day during each assessment period.

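### On the stated intervals, baseline CGM falls on weekdays and post-intervention CGM on a weekend, so the exploratory before-after glucose change cannot be attributed to training alone

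*Protocol article*

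**What the plan says.** The CGM schedule has to be assembled from several sections of the protocol article.

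- Study Design: "All participants will begin supervised training on a Monday".
- Supervised Exercise Training: "10 days after completing baseline testing, eligible participants will begin the 2-week supervised exercise training". The programme is "10 sessions of exercise performed over a 12-day period (ie, Monday to Friday over 2 weeks with Saturday and Sunday as rest days"). In Table 1 the home days are 4, 7 and 9, so day 10 is supervised.
- Baseline Testing and Randomization: CGM volunteers "will return to the laboratory 3 days after the preassessment for insertion of a continuous glucose monitor (CGM"). The aim given there is exploratory: whether CGM can pick up change in glucose control in this population. On the length of wear and on food, the same section states: "The CGM will be worn for 2 consecutive days, and participants will be provided with a standardized diet".
- Continuous Glucose Monitor: "CGM data will be collected for 24 hours at baseline and beginning approximately 24 hours after the last day of supervised training". For interpretability, "each participant will consume the same meals at the same times of the day during each assessment period". The outcomes include average glucose, post-meal spikes and glycemic variability.
- Biochemical Variables: blood is drawn fasted and again 30 minutes after a 75 g glucose drink. "Postintervention samples will be obtained approximately 48 hours following the last supervised training session and at 12-month follow-up".

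The fourth objective and the Proposed Data Analyses section also set a comparison of CGM results between HIIT and MICT.

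**The concern.** Whether CGM can detect change is a before-after question. If every before window falls on working days and every after window on a weekend, a difference in sleep, waking time or everyday activity between those days appears as a change in glucose, or masks one. Randomisation does not help, because the shift is common to both arms and remains in each arm's own change. The protocol fixes meals and meal times in the CGM periods but says nothing about activity or sleep.

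A second, smaller issue concerns the glucose drink. At baseline it is taken three days before the sensor goes in. After the intervention it is due at about the time the CGM window closes. If it falls inside, the post window holds an excursion with no baseline counterpart, and the spike and variability outcomes are the most exposed.

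**Working it through.** **Calendar.** Set training day 1 to a Monday.

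- Check on the plan's own figure: Monday of week 1 to Friday of week 2 is 11 days later, so 11 + 1 = 12 calendar days, as stated.
- Baseline testing: Monday - 10 days = Friday.
- Sensor insertion: Friday + 3 days = Monday. Removal: Monday + 2 days = Wednesday.
- Last supervised session: Monday + 11 days = Friday.
- Post-intervention CGM start: Friday + about 24 h = Saturday. End of the 24-hour window: Sunday.
- Post-intervention blood sampling: Friday + about 48 h = Sunday.

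Weekend hours: 0 of 48 in the baseline wear and 24 of 24 in the post-intervention window. The latter count is the same for a last session at 08:00, 12:00 or 17:00.

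**Sensitivity to the baseline gap** (insertion assumed at 09:00):

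| Gap from baseline to day 1 | Insertion day | Weekend hours in 48 h baseline wear |
|---|---|---|
| 8 days | Wednesday | 0 |
| 9 days | Tuesday | 0 |
| 10 days (as stated) | Monday | 0 |
| 11 days | Sunday | 15 |
| 12 days | Saturday | 39 |
| 13 days | Friday | 33 |
| 14 days | Thursday | 9 |

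**Position of the drink.** At the nominal times it comes 48 - 24 = 24 h after the CGM start, which is the end of the window. However, blood is taken after an overnight fast, and the Anthropometric and Demographic Measures section places the post-intervention measurements in the morning. Assume a drink at 08:00 on Sunday and a last session at clock hour h on Friday. The window opens at hour h on Saturday, so the drink falls 24 - (h - 8) = 32 - h hours into it:

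| Last session | Drink, hours into window | Hours from drink to end of window |
|---|---|---|
| 08:00 | 24 | 0 |
| 12:00 | 20 | 4 |
| 17:00 | 15 | 9 |

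At baseline the drink is on Friday and insertion on Monday, so it cannot fall in the wear.

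**Possible size of the drink effect, if it is inside.** The document gives no figure. Assume a triangular 2-hour excursion peaking 2 to 5 mmol/L above the level otherwise seen. Its area is peak x 2 / 2 = 2 to 5 mmol/L x h. Divided by 24 h, this adds 0.08 to 0.21 mmol/L to the mean, plus one extra excursion in the spike and variability measures.

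**The case against.** The case against has several sound parts.

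- A reader might infer that 2 days of wear and 24 hours of data contradict each other. They do not. The first is how long the sensor is worn, stated for the baseline wear only; the second is how long data are collected. The standardised diet covers the day before and the day of each 24-hour period, which fits a 2-day wear.
- A reader might infer that a 2-day post-intervention wear takes in the glucose drink. No section gives the length of the post-intervention wear or the time of that insertion. On the stated times the drink is at the end of the window. Being inside it depends on visit times that are only approximate.
- The pattern need not hold for every participant. About 10 people start on the same Monday and each baseline visit takes about 150 minutes: 10 x 150 / 60 = 25 h if done one at a time. One Friday may not hold a wave, and gaps of 11 to 14 days put some baseline hours on a weekend.
- The substudy is exploratory, with 8 to 10 volunteers per group, and the planned group comparison does not suffer because both arms follow one calendar.

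All of this narrows the point. It does not remove it: the exploratory label explains the absence of a sample size, but the stated aim is still a before-after one, and the stated intervals tie it to the day of the week.

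**Conclusion.** The concern holds in limited form. With the intervals taken as written, before and after coincide with weekday and weekend (0 of 48 against 24 of 24 hours), so the within-arm CGM change cannot be ascribed to training alone. This rests on the 10-day gap being kept. The glucose drink is a possible contaminant of the post window only, dependent on visit times.

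A reader might go further and conclude that the HIIT-MICT comparison is confounded. The documents do not support that: the day-of-week shift applies equally to both arms. Nor can the size of the weekday-weekend effect be stated, since the document gives nothing from which to derive it; a false-positive rate built on an assumed shift would only restate the assumption. The consequence is confined to an exploratory aim in about 20 people. The correction is still worth making because it costs almost nothing and protects outcomes that the protocol names.

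**What to change.** 1. Define one 24-hour analysis window for each assessment. End the post-intervention window before the glucose drink, discard readings from the drink onward, and use the same clock hours at baseline.
2. State when the post-intervention sensor is inserted and how long it is worn.
3. Record and report the weekday of each window, and match weekdays where scheduling allows.
4. Make the baseline-adjusted HIIT-MICT difference the main CGM result. Where weekdays are unmatched, report the within-arm change descriptively and do not attribute it to training.

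The Results section says data collection ended in March 2017, so matching by scheduling can help only a later use of this design. Truncating the window, reporting weekdays and limiting the before-after statement can still be done at analysis.

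Cost: some hours of post-intervention CGM data for some of about 20 people (0 to 9 hours each under the visit times assumed above), the matching baseline hours, and a more modest before-after statement. Moving sensor insertion to the baseline visit would align the weekdays but is not recommended here, because the diet day before monitoring would then contain the fast, the glucose drink and the maximal exercise test.
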